### Participant recruitment

We will recruit participants from the Greater Montreal area by verifying lists of prospective and past patients in our faculty. This will be done directly with the faculty’s clinical staff to reach those patients. Priority will be given to patients treated in recent years who may need to have their old IMOs replaced, e.g., 63 patients from 2010 to 2018 (around eight patients/year). Staff involved in clinical services will mention this study to patients and, if the latter have interest, refer them to our trial coordinator (TC). Patients without implants will be included if they comply with inclusion criteria #4 (two implants in the lower jaw) within the recruitment period.

Recruitment rate will be based on the ability of the researchers to provide treatment rather than participant availability, which is set at three patients/month. Recruiting 37% of the 63 patients available from 2010 to 2018 would reach the planned sample size (*n* = 26). Participants will be assigned to interventions with the recruitment flow, which will take nine months (from the 5th to the 14th month). Recruitment and care provision to participants will be spread over a 9-month period to reduce seasonal variation in their responses.

### Trial interventions

After screening and obtaining patient consent, participants will return to start denture fabrication (Fig. 2). Both denture pairs will be fabricated simultaneously and delivered in random order. Existing attachments will be replaced by Novaloc abutments of adequate cuff height (external margins 1 mm above the mucosa) and yellow/medium retentive matrices.

**Fig. 2 Fig2:**
[figure not shown]
The trial intervention procedures

Participants will come for a first appointment for scanning their existing dentures, with new abutments (manual torque) and attachment housings in place. The first visit will be the same for both conventional and digital pathways and will consist of scanning the patients’ existing upper complete denture and IMO. The existing dentures will be scanned by using an intraoral scanner (Cerec Primescan, Dentsply Sirona, Charlotte, NC, USA). In the lab, the resulting.stl files will be 3D printed using a Max DLP 3D printer (Asiga, Alexandria, Australia).

In a second clinical appointment, the interim printed dentures will be adjusted with wax for the desired lip support, occlusal plane, occlusal vertical dimension (OVD), and centric relation (CR). Secondary impressions (regular PVS – Examix, GC America, Alsip, IL, USA) will be taken under the intaglio to refine fit, with the new abutments and housings in place. Maxillary and mandibular interim printed dentures will be scanned separately and in occlusion. The face of the patients will also be scanned by a face scanner (Shining 3D face scanner, Shining 3D Ltd.).

In the second lab session,.stl files will be superimposed for the digital pathway. Another software (Exocad Full Denture Module, Exocad GmbH, Darmstadt, Germany) will be used to set teeth and denture bases virtually; virtual dentures will be superimposed to the facial images to estimate final results.

Denture bases will be manufactured by a Max DLP 3D printer with Dentca Denture Base Resin (Dentca Inc., Torrance, USA) at 100 μm/layer and supports on the flanges’ facial surface. A 0.3-mm relief will be applied in the sockets dedicated to receive teeth and attachment housings. Following washing in isopropyl alcohol (5 min), dentures will receive Portrait 3D teeth (Dentsply Sirona, Charlotte, USA), treated by the Fuse 3D Denture Bonding System (Dentsply Sirona). Uncured base resin will be used to lute teeth and cured under UV. Final polymerization will take place in a dental polymerization equipment (Flash, Asiga) for 30 min. Dentures will be finished and polished, and sandblasted (50 μm aluminum oxide) in the attachment sockets.

For the conventional pathway, the second lab session will consist of pouring the impressions (type IV stone), mounting the casts in an Arcon semi-adjustable articulator, removing the printed teeth, and replacing them with wax rim and acrylic tooth setup (Portrait, Dentsply Sirona – same shape, size, and shade used for 3D-printed dentures).

A third appointment will be used for wax try-in for the conventional pathway. For the digital pathway, participants will have a chance to appraise their smile on a computer screen (virtual try-in, done remotely) and request modifications.

Denture bases will be manufactured with conventional heat-polymerized resins, and participants will return for a fourth appointment for delivery, including chairside pick-up of attachments (GC Reline resin; GC America Inc., Alsip, USA). Two short-term adjustments will be scheduled 24–72 h and 7 days after delivery, and then weekly until the dentures are comfortable.

In the fourth appointment, the following will be done for the digital pathway: denture delivery, including abutment insertion (torque: 35 Ncm), chairside attachment pick-up, and first adjustments. Chairside pick-up will use a hard reline resin (GC Reline), to be handled as per manufacturer recommendations.

For both interventions, we expect to adjust most dentures at two post-delivery appointments. In a previous RCT on conventional complete dentures, 10% needed more than four appointments, with a maximum of six appointments for a single participant (total *n* = 39) [16].

Participants will be scheduled for outcome assessment at 3 months following the delivery of each denture pair. A 3-month period is enough to elicit stable patient perception of existing dentures but will not induce significant wear/degradation of dental biomaterials or poor fit due to changes in intraoral tissues. Moreover, extending each follow-up from 3 to 6 months is not expected to result in changes of ratings of patient satisfaction with received dentures, even if denture adjustments are part of the 3-month period [32, 33].

### Participant allocation and minimization of bias

Assignment to either experimental or comparator as the first method will take place immediately after delivery adjustments of both denture pairs. The sequence for the interventions will be decided at the individual level following a list of random numbers (1:1 ratio), according to permuted blocks of varying sizes. Randomization will be performed by the trial coordinator (TC; uninvolved with clinical and follow-up procedures) and will take place at the individual level. The TC will retain a list of fabrication methods per denture pair and identify them as #1 and #2, depending on which will be used first. Random allocation to each intervention sequence will be concealed until both denture pairs are ready for delivery.

The TC will be the only person with access to the randomization codes. It is known that gender influences patient perceptions of received dentures, e.g., elderly women tend to give a higher value to esthetics than their male counterparts [34, 35]. Therefore, the sample will be stratified based on male/female, to analyze possible effects of gender on trial outcomes.

Regarding blinding, participants will be unaware of received interventions, and a researcher uninvolved in the clinical procedures will collect outcome data. Blinding will be lifted only after data collection is complete. Since digital manufacturing may have some specific features (like a subtle staircase topography), blinding effectiveness will be verified at each 3-month follow-up. Participants will answer which denture pair is in use, and to grade their conviction of their response from 0 to 10 (“not at all certain” and “extremely certain,” respectively) [36].

### Outcome measures

The primary outcome of this trial will be the general satisfaction of participants with their full dentures, in line with its ultimate goal. In addition, secondary measures will include satisfaction-specific aspects (e.g., chewing ability and esthetics), oral health related quality of life (OHQoL), clinical quality of the dentures, and treatment costs, all based on a public health system perspective.The McGill Denture Satisfaction Questionnaire (MDSQ) [37, 38] will be used to measure overall satisfaction, and satisfaction with specific aspects of the denture—ability to chew, comfort, stability, esthetics (appearance), ability to speak, and ability to clean. Participants will rate their satisfaction on a 100-mm visual analogue scales (VAS) with anchors representing “no satisfaction at all” to “complete satisfaction.” Participants will receive training with VAS before answering the MDSQ. Previous studies have shown good properties for the MDSQ. Besides good internal consistency and reproducibility [38, 39], its ability to discriminate between different clinical conditions denotes good construct validity [38, 40, 41]. At the last follow-up, participants will be asked about which denture pair they prefer, if any, and their reasons.OHQoL: This construct, conceptualized as the “subjective evaluation of the individual’s oral health, functional well-being, emotional well-being, expectations and satisfaction with care, and sense of self” [42], will be assessed by the Oral Health Impact Profile for Edentulous Patients (OHIP-EDENT) questionnaire. OHIP-EDENT is a short version (20 questions) of the original 49-question OHIP (Oral Health Impact Profile) tested specifically with edentulous individuals [43]. Questions can be grouped into subscales, corresponding to domains/dimensions of perceived impact, including functional limitation or social disability. This short version shows good reliability and discriminant validity, akin to the original OHIP [43]. Despite the seven original subscales, a four-domain model based on recent factor analysis studies will be used [44, 45].Clinical denture quality: This trial will use the Functional Assessment of Dentures (FAD) instrument to assess denture quality [46, 47]. FAD is composed of questions about relevant clinical parameters, including dental occlusion/articulation, denture retention, and stability. A single dentist will apply the instrument without removing the dentures from the mouth, which will ensure that s/he cannot see the staircase topography of CAD/CAM fabrication. The color of the denture base materials will be verified at baseline and after 3 months with a Vita EasyShade portable spectrophotometer [48]. Upper dentures will be placed on a black background and three measures will be taken from the center of the palatal vault, at the polished side. Color measures will be expressed according to the CIELCh and CIELab systems. Clinically evident damage (e.g., fractured base or teeth, stains) to denture constituents will be also reported.Cost: Data on both the direct and indirect costs of each fabrication method will be gathered, as done previously [16, 49]. The number of clinical visits for denture fabrication and adjustments will be reported separately, including non-scheduled visits. Total cost per fabrication method will be described in terms of expenses with human resources (time and CAD$) and materials (consumables/equipment use, CAD$). Yearly cost differences, or $(Δ), will be calculated based on the expected lifetime of 5 years for a pair of dentures, by dividing total cost differences by five. After the last follow-up, participants will answer four questions on their willingness-to-pay for each denture pair: (1) If you were to choose A over B, how much are you willing to pay for it? (2) Are you willing to pay the $(Δ) to have A over B? (3) Are you willing to pay the $(Δ) to have A over B by monthly installments (12 months)? (4) Do you think that a public health plan should cover the cost of these treatments? Both or only A or B.

The cost-effectiveness of both methods will be compared by using overall patient satisfaction to measure the effect of interventions. Economic analysis will have the perspective of the public health system of Quebec. All expenditures and resources through all stages of dental care (from clinical exam to denture adjustments) will be included, considering a short-term/3-month time frame. Results will be expressed by the incremental cost-effectiveness ratio (ICER).5.Adverse effects: All adverse events during the RCT will be recorded at each post-delivery appointment and follow-up. Common events, i.e., mucosal injuries and difficulties with new dentures, will be rated on a three-point ordinal scale [50]. More uncommon (nausea, change in taste and lingering speech difficulties) and rare events (allergy to denture materials) will be reported on a binary scale.6.Choice of overdenture and patient experiences: A qualitative analysis will be carried out to better understand patients’ perception of CAD/CAM dentures and to find out any emergent themes besides (1) patients’ reasons for choosing a specific denture pair and (2) their experience of using a 3D-printed IMO. By adopting a descriptive approach, individual semi-structured interviews will be carried out to obtain an in-depth understanding of patients’ experiences and preferences [51].

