**Methods/design:**

We will recruit 26 completely edentulous participants (any sex/gender) based on the following eligibility criteria: age ≥ 60 years, no tooth extraction in the past 12 months, two implants in the lower jaw, and need for new dentures in both jaws. Each participant will receive two denture pairs, either manufactured by 3D printing or traditionally, to be worn in a random order. A timeline of 3 months with each denture pair will be considered for outcome assessment (total: 6 months). Patient satisfaction with dentures will be measured by the McGill Denture Satisfaction Questionnaire. We will evaluate other patient-reported outcomes (including oral health-related quality of life) as well as clinician-assessed quality and cost. At the end of the trial, participants will choose which denture pair they wish to keep and interviewed about their experiences with the 3D-printed IMO. The quantitative and qualitative data will be incorporated through an explanatory mixed-methods strategy. A final quantitative assessment will happen after 12 months with the preferred IMO to assess the long-term performance and maintenance needs.

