### Objectives and hypothesis

We aim to conduct the first mixed-methods cross-over RCT to determine the efficacy and patients’ experience with 3D-printed implant-retained mandibular overdentures (IMO), compared to the traditional method, for independently living edentulous seniors who have two implants in the anterior mandible, as purported by the McGill Consensus on Implant Overdentures [26]. Our null hypothesis is that IMOs produced by computer-aided design and 3D printing are as satisfactory to edentulous seniors as those fabricated using traditional methods.

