## Methods

### Design and setting

This mixed-methods cross-over RCT will compare one experimental intervention (CAD/CAM dental prostheses) versus an active comparator (conventional denture fabrication methods). Outcome assessment will take place 3 months after each intervention, up to a total follow-up of 6 months. This will be a single-center RCT, conducted at the Faculty of Dental Medicine and Oral Health Sciences, McGill University (Montreal, Canada). The creation of this report adhered to the guidelines outlined in the Standard Protocol Items: Recommendations for Interventional Trials (SPIRIT) [28]. Figure 1 illustrates the standard protocol items diagram as suggested by SPIRIT, while the SPIRIT checklist for this study is provided in Additional file 1.

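### The objective and null hypothesis name the mandibular overdenture alone, but the trial switches both dentures together, so its result belongs to the denture pair

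*Protocol article*

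**What the plan says.** Objectives and hypothesis sets the aim as efficacy and patient experience with "3D-printed implant-retained mandibular overdentures (IMO), compared to the traditional method", and the null hypothesis follows in the same terms: "IMOs produced by computer-aided design and 3D printing are as satisfactory to edentulous seniors" as those made conventionally. The Background and Discussion paragraphs of the abstract also pose the question for the printed IMO.

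The treatment is wider. The abstract's methods paragraph states: "Each participant will receive two denture pairs, either manufactured by 3D printing or traditionally, to be worn in a random order". Eligibility criteria requires patients who want an upper denture as well as a lower IMO. Trial interventions describes both pathways for the two arches together. Under Participant allocation and minimization of bias, the coordinator records the fabrication method by pair. Design and setting is worded broadly, as "one experimental intervention (CAD/CAM dental prostheses) versus an active comparator (conventional denture fabrication methods".

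Under Outcome measures, the primary outcome is the "general satisfaction of participants with their full dentures". Preference and willingness to pay are asked for the pair. For colour, "Upper dentures will be placed on a black background", with readings from the palatal vault.

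The final choice is described in two ways. The preference question in Outcome measures and the long-term follow-up paragraph refer to a denture pair. The title of the sixth outcome and the 6-month visit in Outcome assessment timeline refer to an overdenture.

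**The concern.** A hypothesis about one device is to be answered by a contrast in which two devices change at once. If the printed pairs score higher, the protocol's wording leads to the conclusion that printed IMOs are more satisfactory, although the gain could lie wholly or partly in the upper denture. If the scores do not differ, the wording leads to the conclusion that printing makes no difference to the IMO, although opposite effects in the two arches could have cancelled. The Discussion section expects the results to inform the provision of IMOs under public programmes, so an attribution the design cannot support could reach policy readers.

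**Working it through.** The plan gives no figure on this point to reproduce. The question is what the design identifies, and it can be settled from the stated treatment structure.

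**Inputs**
- Hypothesis: IMO only (Objectives and hypothesis).
- Unit that switches: the pair, one method per pair (abstract; Trial interventions; Participant allocation and minimization of bias).
- Primary score: satisfaction with the full dentures, with no separate score by jaw stated (Outcome measures).
- Minimal important difference: 10 mm on the 100-mm scale (Sample size estimation).

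**Step 1: treatment indicators.** Let U = 1 if the upper denture in use is printed and 0 if conventional. Let L be the same for the lower. Four combinations are possible: (0,0), (1,0), (0,1) and (1,1). In this trial only (0,0) and (1,1) occur. U equals L for every participant in every period, so their correlation is 1.

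**Step 2: what the contrast estimates.** Write the expected rating, apart from period and participant effects, as m + a·U + b·L + c·U·L. Here a is the effect of printing the upper, b the effect of printing the lower, and c any interaction. Then

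printed pair − conventional pair = (m + a + b + c) − m = a + b + c.

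This is one estimable quantity for three unknowns. A regression that included both U and L would be singular.

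**Step 3: what an observed result allows.** With c = 0 for simplicity, and with splits chosen only for illustration:

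| Pair difference | Upper (a) | IMO (b) |
|---|---|---|
| 10 mm | 10 | 0 |
| 10 mm | 5 | 5 |
| 10 mm | 0 | 10 |
| 10 mm | 15 | −5 |
| 10 mm | −5 | 15 |
| 0 mm | 10 | −10 |
| 0 mm | 0 | 0 |

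Every row agrees with its observed difference, and the data cannot choose between rows that share one.

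**Step 4: does sample size help?** No. More than the 21 required or 26 enrolled participants would tighten the estimate of a + b + c. It would give no information on b alone.

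**Step 5: would a rating by jaw help?** Only in part. A separate rating of the lower denture would still be given while the upper has the same fabrication method, so the upper could influence it. The score would be specific to the jaw, but the treatment contrast behind it would still be the pair.

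**The case against.** The strongest reply is that the pair is the treatment. The two dentures are built to work against each other: vertical dimension and centric relation are set jointly, and they are scanned in occlusion. The economic comparison is by fabrication method, and the practical question is whether to adopt a workflow. The pair is disclosed in the abstract, the eligibility criteria and the allocation section, and the design section already speaks of prostheses generally. IMO may simply be shorthand for the treatment that includes one. All of this stands, and it is why the pair contrast should be kept. It also means that the objective and hypothesis should name the pair.

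Several stronger readings are tempting, but the documents do not support them:
- *The primary comparison is invalid, or nothing useful is tested.* The printed-versus-conventional pair contrast is randomised and relevant to the decision. Only its attribution to the IMO fails.
- *Nothing in the outcome list concerns the IMO separately.* The sixth outcome and the interviews ask about experience with the printed IMO, though qualitatively. The items of the satisfaction and denture-quality instruments are not reproduced, so the absence of items by jaw cannot be asserted. Such items would not undo the joint switching in any case.
- *Measuring colour on the upper denture is a fault.* The stated target is the colour of the base materials, and the text does not present it as an IMO result.
- *Printing acts mainly through the upper denture.* The protocol gives no effect by arch, so the direction and size of any misattribution are unknown.

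**Conclusion.** The point holds as a mismatch between the stated question and the contrast that answers it. The objective and null hypothesis concern the IMO; the trial estimates the combined effect of a printed maxillary denture and a printed IMO. The IMO's own share is not identified at any sample size. The consequence lies in what may be concluded: randomisation, sample size and primary analysis are unaffected. No magnitude of bias can be given, because the documents contain no effects by arch and the splits shown in the working are illustrations. The finding rests on the joint switching that the article states, so a fuller protocol that scored satisfaction by jaw would not remove it.

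**What to change.** 1. Restate the objective and null hypothesis for what is randomised. For example: mean overall satisfaction is the same with 3D-printed as with conventionally made denture pairs, each consisting of a maxillary complete denture and a two-implant mandibular overdenture. Word the planned conclusions the same way, in line with Design and setting.
2. In the sixth outcome and at the 6-month visit, describe the final choice as one of denture pair, to match the preference question and the long-term follow-up paragraph.
3. Report the colour result as measured on the maxillary denture base.
4. Leave the primary rating unchanged.

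These edits cost only wording and can be made before reporting, although recruitment has been open since January 2024.

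Optionally, add one visual analogue item for the upper and one for the lower denture after the existing questionnaire. They would be supportive only and should not be the basis for a claim about the IMO, because they do not separate the effects of the two arches. Their cost is a little participant time, items outside the validated form, further secondary comparisons, and possibly missing values for participants already seen.
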